## Summary

Fast-track/rapid recovery/Enhanced Recovery After Surgery (ERAS) programs have shown to be proven both safe and effective in joint replacement surgery (JRS), to the degree where same-day surgery have been tested in selected cases. A transition of the minor partial knee replacement (PKR) procedure, compared with the alternative and more commonly used total knee replacement (TKR) for knee osteoarthritis (OA), into a same-day regime seems reasonable. Especially as PKR is reported to have lower risk of short-term complications than does TKR.

The aim of this study is to assess efficacy, patient satisfaction and safety outcome measures for PKR when using a same-day surgery protocol in a Swedish healthcare context where ERAS programs for JRS nowadays are considered common ground.

With no preselection of patients, all PKR cases by one high-volume surgeon will chronologically be scheduled as the first morning case during one consecutive year, and thereby be included in this observational study. In order for discharge, strict post-surgery criteria will have to be met. Patient characteristics will be documented and at a 3-month follow-up, percentages of discharge on day of surgery (DOS), patient satisfaction, adverse events (AEs) and readmissions for any cause will be evaluated.

The thesis is that the same-day surgery will be both feasible and safe as the general conception in the medical team prior to this study has been that the PKR patients, everything else equal, above all are more confident with their knee post-surgery than those that have had a TKR procedure done. As the protocol has become standard practice, the aim of this study will be to observe, document, and analyse the overall positive effects we believe this new routine has achieved.

## Background and rationale

It is fair to say that a general shortening of LOS, including JRS, started off in the US, where the healthcare structure and financial environment differs substantially from e.g. Europe. Henrik Kehlet, a Danish orthopedic surgeon, is considered the first in trying to target all aspects of the perioperative care with the aim of reducing cost and complications, including the use of modern anesthetic techniques and multimodal analgesia with less morphine utilization. These programs come in many names, such as Fast-track, Rapid Recovery or Enhanced Recovery after Surgery (ERAS) as often referred to in Europe where they have been widely spread, not least through JRS register channels.

The PKR procedure may be considered a candidate for same-day surgery, especially as the procedure seems to have a lower risk of short-term complications than does TKR. A recent US database study comprising 169,406 patients who had had a JRS done reported no difference in readmission when comparing the inpatient and the outpatient group, even after adjusted for comorbidity. Data on PKR exclusively is hard to find, but one large retrospective study by Bovonratwet et al compared 568 outpatient and 5312 inpatient PKR cases between 2005 and 2015 which reported no difference in 30-day readmission rate and concluded that same-day surgery can be considered in carefully selected patients. One recent randomized controlled trial (RCT) of 40 patients have shown similar results, as have observational studies.

One observational study from the US by Berger et al showed already ten years ago that 94% of 25 consecutive PKR cases were discharged on DOS with no AE/readmission during a 3-month follow-up. The same group have later reported similar results in 105 unselected cases, including 14 patients classified as ASA 3. Two recent PKR studies, each with their unique pre-selected inclusion criteria, one from the United Kingdom NHS that included 72 patients and one from France that included 50 patients, reported 85% and 94% discharge

on DOS respectively. One RCT from the Netherlands compared same-day surgery to a more traditional fast-track protocol in 40 pre-selected PKR cases and reported 90% discharge on DOS in the same-day surgery sub-group.

Although it is hard to coin one definition of a fast-track/rapid recovery/ERAS program, perhaps it is not even to strive for as every practice has its own unique settings. Though, the essence is to find a common thread in the perioperative regime in order for optimizing patient safety and comfort, with unit cost-efficiency at the same time.

As of today, still very little is written about same-day surgery procedures in the literature. With the primary objective to examine the evidence regarding the safety and feasibility of performing THR, TKR, or PKR in an outpatient setting a systematic review was recently conducted by Pollac et al; out of 805 studies only 17 passed the inclusion criteria, neither of which were randomized controlled trials, only four were controlled but lacking patient characteristics and therefore, needless to say, unadjusted.

Therefore, the intention is to conduct an observational study on efficacy and safety in patients receiving a PKR surgery following a same-day surgery protocol in a Swedish healthcare context, where ERAS programs for JRS nowadays are considered common ground.

# Objectives

## Primary aims

The primary aims of this 3-month follow-up study to assess safety outcome measures for a same-day PKR surgery protocol, including AE and readmission for any cause.

## Secondary aims

Secondary aims of this study will be to assess efficacy measures such as who and how many will be discharged on DOS, and what burden will instead be allocated to the out-patient department.

# Patients and methods

## Study design

### *Cohort study – Level of evidence, 2*

This observational study will be conducted at Trelleborg hospital, a public hospital in Region Skåne, a county council in the south of Sweden, performing around 1.500 JRSs each year. The efficacy and safety aspects of the same-day surgery protocol to be assessed is in fact only a slight modification of an existing ERAS protocol that has been used for years at the department.

To best evaluate these measures, the study is pragmatically design as no patient-selection will be done prior to surgery. I.e., all patients, regardless of any medical history, considered for a PKR procedure will also be informed prior to surgery by the multidisciplinary team (nurse, surgeon, anaesthesiologist, and physiotherapist) that if the surgery is to be scheduled in the morning, he/she will then follow a same-day surgery protocol and will likely be discharged to home later the same day.

The actual “recruitment” will be done in the following manner: All of one high-volume surgeon’s first morning cases during one consecutive year will be dedicated to a PKR patient, and thereby also included in this cohort study. The slots will filled continuously as the patients are put up for surgery. When all slots have been occupied within one week any additional PKR cases will be assigned to surgery later in the day in the same week, as will all the TKRs and the THRs this year, and consequently not taking part in the study. (It must be emphasized that, for the fairness of all patients, the operation scheduling will be put

together on a weekly bases, in a strict chronological order, by a team of nurses and without any insight of the surgeon in question.)

A slight modification to an existing ERAS protocol will be used (see below section "*The same-day surgical protocol (in short)*"), in which the patients will be discharged to home on DOS if certain postoperative criteria are met. These are categorized into four dimensions; vital parameters, urinary function, bleeding and mobilization: The vital parameters will be measured and scored by the National Early Warning Score (NEWS), where the threshold for discharge will be set to zero ( NEWS 0). The urinary function algorithm for discharge on DOS is, in short, if no need for catheterization less than 200 ml of residual volume after spontaneous void. A compression stocking will be removed six hours post-surgery and if no ongoing bleeding discharge can be considered. Last but not least, a physiotherapist will evaluate whether basic activity of daily living (ADL) can be performed in a safely manner. The surgeon will phone the patient the day after surgery for an early check. At 3-month follow-up an evaluation of efficacy, AE and readmission will be done.

## Patients

### *Inclusion criteria*

- With no preselection of patients, all of one surgeon's UKA morning cases during one consecutive year

### *Exclusion criteria*

- Patients who will have a UKA procedure done by any other surgeon
- Patients who will have a simultaneous bilateral UKA procedure
- Patients not scheduled as the first morning case\*

*\*The scheduling procedure will be done in a strictly chronological manner on a weekly bases without any involvement of the surgeon/author.*

### *Withdrawal criteria*

Not applicable

## Perioperative conditions

### *The operating room and medical regimes*

The operations will be performed using a clean-air enclosure with vertical air-flow. Three doses of intravenous antibiotic will be given each patient within the first 24 hours of surgery starting preoperatively (a total of 6 g isoxazolympenicillin or if allergic towards penicillin 1.2 g clindamycin), as well as corticosteroids (8 mg of betamethasone) and antifibrinolytics (10 mg/kg of tranexamic acid). 300 ml of local infiltration analgesia (LIA) will be administered (300 mg of ropivacaine, 30 mg of ketorolac and 0.5 mg of adrenaline). Each patient will from day 1 be given subcutaneous injections of 40 mg low-molecular-weight heparin (enoxaparin sodium) as thromboembolic prophylaxis.

### *Implant design and surgical technique*

The implant design to be used in this study will be the LINK® Sled prosthesis, Link. The procedures will be done using a mini incision, i.e. not everting the patella.

## The same-day surgical protocol (*in short*)

### *Planning stage*

At the routine medical check 2 weeks prior to surgery the medical team will be notified of which patients will be scheduled for morning surgery and the patients will be given both oral and written information about the same-day surgery routine.

### *Day of surgery*

The perioperative protocol is aimed at optimizing for rapid mobilization by avoiding early postoperative numbness (general anesthesia), urinary retention (no catheter), bleeding (antifibrinolytics), stress (corticosteroids) and discomfort (local infiltration anesthesia).

The dimensions and their respective criteria for discharge are the following:

- Vital parameters; measured and scored by the National Early Warning Score (NEWS), with the threshold set to NEWS 0
- Urinary function; less than 200 ml of residual volume after spontaneous void will be required
- Bleeding; no wound leakage will be allowed
- Mobilization; a physiotherapist will make sure the patient is able to perform ADL in a safe manner before discharged can be considered

### *Day after surgery*

The surgeon will phone the patient to answer any questions that may have arisen since the surgery and to evaluate the following variables:

- If still positive to have been discharged on DOS, i.e. would have chosen it again and could recommend it to others?
- Degree of wound leakage?
- Degree of pain?

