## 3-month follow-up

Patient characteristics such as age, sex, BMI, ASA and Charnley class will be used in this study. Apart from whether or not the patient did discharge on DOS and his/her experience from the routine (evaluated by a phone the day after surgery), at 3-month post-surgery the following parameters will also be evaluated:

- Any additional appointments to the outpatient department
- Any complications at the 3 month doctor's appointment
- 30-day adverse events and/or readmission for any cause
- 90-day adverse events and/or readmission for any cause

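### Satisfaction, part of the stated study aim, rests on one day-1 phone item asked by the operating surgeon-investigator, and patients not discharged on the day of surgery cannot answer it

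*Protocol*

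**What the plan says.** The Protocol Summary states the aim as follows: "The aim of this study is to assess efficacy, patient satisfaction and safety outcome measures for PKR when using a same-day surgery protocol". It goes on to say that "at a 3-month follow-up, percentages of discharge on day of surgery (DOS), patient satisfaction, adverse events (AEs) and readmissions for any cause will be evaluated". Neither Primary aims (safety) nor Secondary aims (who and how many go home on DOS, and the load on the outpatient department) mentions satisfaction.

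The section Day after surgery describes the measurement in these terms: "The surgeon will phone the patient to answer any questions that may have arisen since the surgery and to evaluate the following variables". Three variables follow. Wound leakage and pain are two of them, and the one that bears on satisfaction is "If still positive to have been discharged on DOS, i.e. would have chosen it again and could recommend it to others". The section 3-month follow-up agrees on the timing, since it refers to "his/her experience from the routine (evaluated by a phone the day after surgery". The parameters it lists for the 3-month evaluation begin with "Any additional appointments to the outpatient department" and continue with complications and with 30-day and 90-day adverse events or readmission. None concerns satisfaction.

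On who asks: Surgeons says that a single surgeon does all the operations, Disclosures identifies the investigator as that surgeon, and Data management makes the investigator responsible for compiling and analysing the data.

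**The concern.** Two features of the measurement matter.

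- **Who can answer.** The item asks about having been discharged on DOS. A patient kept overnight was not, and no alternative item is given. The patients for whom the routine did not work are those without a usable answer. This sits badly with Study design, which stresses that no patients are selected, and with Patient information, which warns against including only the most favourable patients.
- **Who asks.** The question is put orally, without anonymity, by the person who operated, who runs the study, and whose Summary already expects positive effects. Patients may find it hard to give that person a critical answer.

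At stake is how a high satisfaction percentage can be read. It could pass for the view of an unselected cohort when it describes only the patients for whom same-day discharge succeeded, as told to their surgeon. The primary safety aim is not affected.

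**Working it through.** The Protocol gives no satisfaction rate, sample size or denominator, so there is no planned figure to reproduce. The check has two parts.

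**1. The sections side by side**

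| Protocol section | What it says about satisfaction |
|---|---|
| Summary | Part of the aim; among the items evaluated at 3 months |
| Primary aims, Secondary aims | Not listed |
| Study design | Day-1 call described as an early check; efficacy, adverse events and readmission at 3 months |
| Day after surgery | One item, tied to DOS discharge, asked by the surgeon |
| 3-month follow-up | Experience taken from the day-1 call; no satisfaction item in the 3-month list |

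The methods sections agree with each other. The Summary and the listed aims differ on whether satisfaction is an objective, and the Summary is unclear on when it is measured.

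**2. Effect of having answers only from discharged patients**

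Inputs:
- d, the share discharged on DOS: 0.85 and 0.94, from the UK and French series cited under Background and rationale. Both were pre-selected and this cohort is not, so using these values here is an assumption.
- s, the share positive among those discharged: assumed 1.00, then 0.90.
- k, the share who would be positive among those kept in: assumed 0, 0.50, or equal to s.

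Formulas:
- Whole-cohort share = d × s + (1 − d) × k
- Overstatement = s − whole-cohort share = (1 − d) × (s − k)

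| s | k | Whole cohort, d = 0.85 | Overstated by | Whole cohort, d = 0.94 | Overstated by |
|---|---|---|---|---|---|
| 1.00 | 0 | 0.850 | 15 points | 0.940 | 6 points |
| 1.00 | 0.50 | 0.925 | 7.5 points | 0.970 | 3 points |
| 1.00 | 1.00 | 1.000 | 0 | 1.000 | 0 |
| 0.90 | 0 | 0.765 | 13.5 points | 0.846 | 5.4 points |
| 0.90 | 0.50 | 0.840 | 6 points | 0.876 | 2.4 points |
| 0.90 | 0.90 | 0.900 | 0 | 0.900 | 0 |

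Worked line: with d = 0.85, s = 1.00 and k = 0.50, the cohort share is 0.85 × 1.00 + 0.15 × 0.50 = 0.925, so a reported 100% is 7.5 points too high.

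The overstatement depends on k, which the planned item cannot supply. If fewer patients go home on DOS than in the cited series, 1 − d grows and so does the possible error. The table covers only the restriction to discharged patients. The Protocol offers nothing from which to size the effect of the surgeon asking.

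**The case against.** A fair defence has several parts.

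- **Timing.** A reader might infer that the Summary promises satisfaction measured at 3 months and that the methods break the promise. The text does not support this firmly. The same sentence also lists DOS discharge, which is known on day 0, so it may only mean that results are compiled at 3 months. The follow-up section states the day-1 timing openly. What remains is loose wording to be aligned.
- **Day 1 is defensible.** Experience of going home the same day is well recalled after the first night. A question at 3 months would mix in the result of the knee. Nor can it be said that early timing flatters the result: day 1 may be near the worst pain, and opinions could move either way by 3 months. This stands.
- **Leading wording.** The section lists variables to evaluate and is not shown to be the script read to patients. Leading wording is possible, not established.
- **Denominator.** The call goes to the patient, without restriction to those discharged. No denominator is fixed, and that detail is commonly left to a statistical analysis plan, which is not at hand. This stands as far as analysis goes. It does not supply a question that a patient kept overnight can answer, and no analysis plan can recover answers never collected.
- **Weight.** Satisfaction is not a listed aim, and the analysis is descriptive with no comparison. That limits the importance of the point, but the Summary still names satisfaction in the study aim.

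**Conclusion.** The point holds as a limited, inexpensive improvement. Satisfaction belongs to the aim in the Summary, is missing from the listed aims, and depends on one non-anonymous item asked by the surgeon-investigator that does not fit patients kept in.

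An estimate that is too favourable is likely, because the restriction to discharged patients and the identity of the caller would both be expected to act in that direction. A reader might go further and call the upward bias a fact, or say that a reported 100% would really be 85% to 94% of the cohort. The document shows neither. The second statement holds only if no patient kept in is positive. With every discharged patient positive, the overstatement runs from 0 to 15 points: 6 to 15 with no patient kept in positive, 3 to 7.5 with half, and none if the groups answer alike. All of this assumes that the discharge shares of two pre-selected series apply here.

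**What to change.** - Keep the surgeon's call as a clinical check.
- Record satisfaction with the routine through a short, neutrally worded, self-completed item given to every cohort patient, including those kept overnight.
- Report the number satisfied over all cohort patients, and separately for those who did and did not go home on DOS. State how many did not answer.
- List satisfaction under Secondary aims.
- Make the Summary and the methods agree on when it is measured. An early item alone, or an early item repeated at the existing 3-month appointment, would both serve. Moving it wholly to 3 months is a trade-off, since it would partly measure something else.

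The cost is a one-page form, some Protocol wording and some non-response. Because patients are informed of the routine but not asked to take part, the form must also be covered in the ethics application, which the Protocol says has still to be made. No extra visit is needed.

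### The only satisfaction item combines two judgements, so a non-positive answer does not show which one the patient rejected

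*Protocol*

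**What the plan says.** The Summary states: "The aim of this study is to assess efficacy, patient satisfaction and safety outcome measures". It lists what will be evaluated as "percentages of discharge on day of surgery (DOS), patient satisfaction, adverse events (AEs) and readmissions for any cause will be evaluated".

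The protocol provides one source for satisfaction. Under Day after surgery, the plan for the call is that "The surgeon will phone the patient to answer any questions that may have arisen since the surgery and to evaluate the following variables". The first variable is whether the patient remains positive about having gone home on the day of the operation, which the item explains as "would have chosen it again and could recommend it to others". The other two variables in that call are wound leakage and pain. The section on 3-month follow-up refers back to the same call for the patient's view: "his/her experience from the routine (evaluated by a phone the day after surgery"). Its own four parameters are extra outpatient appointments, complications at the doctor's visit, and adverse events or readmission at 30 and at 90 days. None of them measures satisfaction.

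On how patients enter the pathway, the study design section says that "if the surgery is to be scheduled in the morning, he/she will then follow a same-day surgery protocol". Nurses fill the morning slots chronologically, week by week.

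**The concern.** Wanting same-day discharge again for oneself and recommending it to others are separate judgements. A patient with good help at home might gladly repeat it and still hesitate to recommend it to people in general. Another might think it a sound routine but not want it again. The item puts both judgements into one variable, and nothing else in the data collection could tell such patients apart.

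This is a matter of data collection. If one joint answer goes on the form, no later analysis plan can recover the two components. It also sits awkwardly with the section on patient information, which says that the study should evaluate the routine and perhaps improve it. The patients who are not positive are the ones who could show what to improve, and their answers carry the least information.

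A smaller point of wording is that the first half speaks of choosing again, whereas the design section describes assignment by slot and no choice between pathways.

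**Working it through.** **Inputs.** The definition of positive comes from Day after surgery. The protocol gives no expected satisfaction rate and no sample size, so there is no figure of its own to reproduce. All rates below are assumptions chosen for illustration.

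**Step 1: how the item classifies patients.** The definition joins its two conditions with *and*:

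| Would choose again | Would recommend | Joint item |
|---|---|---|
| yes | yes | positive |
| yes | no | not positive |
| no | yes | not positive |
| no | no | not positive |

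The first row is unambiguous. The other three fall into one category.

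**Step 2: from the halves to the joint rate.** Let *a* and *b* be the shares agreeing with each half. The joint share lies between max(0, *a* + *b* − 1) and min(*a*, *b*).

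- *a* = *b* = 0.90: lower limit 0.90 + 0.90 − 1 = 0.80; upper limit 0.90.
- *a* = *b* = 0.85: lower limit 0.85 + 0.85 − 1 = 0.70; upper limit 0.85.

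The lower limit needs the two groups of refusers to be entirely different people. In the first case, 10% reject only one half, another 10% reject only the other, and nobody rejects both. If the two answers were independent, the joint rate would be 0.90 × 0.90 = 0.81. Two attitudes to the same discharge are probably positively related, which would put the joint rate between 81% and 90%.

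**Step 3: from the joint rate back to the halves.** If a joint rate *p* is observed, each half lies between *p* and 1, and the two halves sum to at most 1 + *p*.

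| Joint rate *p* | Range for each half | Largest possible sum of the halves |
|---|---|---|
| 0.95 | 95% to 100% | 1.95 |
| 0.85 | 85% to 100% | 1.85 |
| 0.60 | 60% to 100% | 1.60 |

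Little is lost when nearly everyone is positive. The loss grows as the joint rate falls, which is when one would most want to know the reason.

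**Step 4: the wording about choice.** The design section makes the pathway follow from the slot: a morning patient "he/she will then follow a same-day surgery protocol and will likely be discharged to home later the same day". The slot follows from the order of listing. Nothing in the protocol describes the patient selecting between same-day and later discharge. The item nevertheless asks about repeating a choice.

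**The case against.** The strongest reply is that the item means what it says. Positive is defined as both conditions together, so a patient who meets only one of them is simply not positive. That stands, and it rules out three stronger conclusions that a reader might draw.

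- *That the rate cannot be interpreted.* It can. A joint yes means both, and the joint rate bounds each half from below (Step 3).
- *That a patient with mixed views has no valid answer.* Under the printed definition the answer is not positive. What is lost is the reason.
- *That the same patients could produce a rate up to 100%.* This would require reading the definition as either condition, which replaces the printed *and* with *or*. The text does not support that.

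Two more replies have weight. First, the section gives the protocol in short and lists variables, perhaps not the verbatim question. No passage says that the halves will be recorded as one yes/no or reported as one percentage. Scoring and tabulation may be set out in an analysis plan or data form that is not at hand, so their absence is no fault. The point concerns only the variable as the protocol defines it.

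Second, a reader might infer that patients were denied a choice. The documents do not go that far. They describe no choice, but do not say whether a patient could decline same-day discharge or ask for another slot. The statement that patients are not asked to participate concerns the study. The phrase can also be taken hypothetically, as asking whether the patient would want the same again. On that reading the wording is loose but usable.

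Finally, satisfaction appears in the Summary but under neither Primary aims nor Secondary aims, and no comparative analysis is planned.

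**Conclusion.** The point holds as a modest improvement to measurement. The study's only satisfaction variable merges two judgements. Its positive answers are clear; its mixed and negative answers are not, and a joint record cannot be separated afterwards. With an assumed 90% agreement on each half, the joint rate could be 80% to 90%; with 85% it could be 70% to 85%. In both cases the low end is extreme. These figures rest wholly on the assumed rates and on the item being recorded jointly, as its definition suggests. The mismatch between asking about a choice and a slot-assigned pathway is secondary.

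No conclusion on the stated aims of safety, discharge on the day of surgery and outpatient burden depends on this item. The consequence is confined to a descriptive result on patient satisfaction.

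**What to change.** Under Day after surgery, replace the joint item with two yes/no answers, recorded separately:

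1. Would the patient want same-day discharge if having the operation again?
2. Would the patient recommend same-day discharge to others?

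Report the two percentages separately, with patients discharged on the day of surgery as the stated denominator, since the item by its wording applies only to them. Putting the first question as a preference also removes the reference to a choice that the protocol does not describe. The joint rate can still be derived from the two answers, so nothing is given up.

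The cost is one more question in a call that already takes place and one more row in the results.
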